### 2.8. Randomisation

Randomisation was conducted at the school level after baseline data were collected. This study was conducted in nine schools (18 classes, one class in each 4th and 5th grade; Figure 1). These schools were matched by size (total number of children) and region (Enzan or Katsunuma area) into four pairs. These pairs and one school with the smallest number of children in Koshu City were randomly assigned to either the intervention group or the control group using random numbers in Microsoft Excel by a researcher who was not directly involved in the implementation. The schools were each assigned a random number, and the school with odd last digits random number in each pair was assigned to the GRAPE intervention group. If the last digit was the same, GRAPE intervention group was assigned by the last second digits random number.

### 2.9. Blinding

Given the nature of the active play programme, it is impossible for teachers to be blinded to group allocation. However, children were not informed about the group differentiations; they were only informed that they would be performing the activity first (intervention group) or later (wait-list control) and, therefore, were blinded to group allocation. In addition, bone mass was measured by research assistants who were unaware of the allocation, PA was assessed using objectively measuring wearable devices, and other outcome data were obtained through self-reporting; thus, reducing potential outcome assessor bias.

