#### 2.4.4. Wait-List Control Group

During the intervention period, the participating school children belonging to the wait-list control group continued their routine school life and only underwent evaluation similar to the intervention group. After the final evaluation in December 2019, the wait-list control group received an activity programme similar to the intervention group but more selective and compact (intervention period: three months).

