## 3. Discussion

This GRAPE study programme is the first study to examine whether voluntary and a very short active play program contributes to increased bone mass and PA in school-aged children. The study is expected to improve the participant’s health indicators, such as increased physical activity and bone mass, mental and social health, and non-cognitive skills, based on the hypothesis that even a small amount of time spent on active play involving jumping will show positive effects on daily repetition. Additionally, the results of this study will help to develop evidence-based effective exercise programmes and health education in schools wherein the effects relative to that in a control group were insufficiently explored. Moreover, by objectively evaluating physical activity using a consumer model wrist-worn accelerometer, it will be possible to validate results, and children will become aware of their own levels of physical activity. However, the interpretation of GRAPE study results will likely be limited owing to the lack of generalizability as the participants were selected from a single rural area. The clusters were small, and there were not enough participants within the clusters, which resulted in a bias between the intervention and control groups. Moreover, as many measures were self-reported by the children, it is possible that measurement errors will occur. Furthermore, because many outcomes will be evaluated, the problem of “multiple comparisons” will need proper attention.

The implementation of this RCT program was possible by building long-term relationships of trust and cooperation between the health promotion section of the city office, the board of education, each school, and researchers through the Koshu project for. Therefore, the findings of this study will be directly returned to the children, guardians, schools and local residents by reporting to the School Health Committee and creating posters or booklets. Thus, this study not only provides novel academic findings but also returns familiar and evidence-based information to the community; therefore, it will be an academically and practically meaningful study.

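### Section 2.9 calls the children blinded although they knew which condition they received, and wrongly counts their self-report among the safeguards against assessor bias

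*Protocol article*

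**What the plan says.** Section 2.9 (Blinding) of the protocol article makes three statements about who knew what.

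- **Teachers:** "it is impossible for teachers to be blinded to group allocation", because of the nature of the programme.
- **Children:** "children were not informed about the group differentiations". They were told only that "they would be performing the activity first (intervention group) or later (wait-list control) and, therefore, were blinded to group allocation".
- **Outcome assessment:** three features are listed in one sentence. The first is that "bone mass was measured by research assistants who were unaware of the allocation". The second is that "PA was assessed using objectively measuring wearable devices". The third, with the conclusion drawn from all three, is that "other outcome data were obtained through self-reporting; thus, reducing potential outcome assessor bias".

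The Discussion returns to self-report once, as a limitation: "as many measures were self-reported by the children, it is possible that measurement errors will occur". It does not connect this to what the children knew about their condition.

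**The concern.** Blinding to allocation means that a participant cannot tell which condition he or she has been given. Section 2.9 infers blinding from a disclosure that tells the child exactly that. It then treats reporting by these same children as a protection against assessor bias.

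What is at stake is the reading of the self-reported secondary outcomes. The Introduction's hypothesis covers mental and social factors as well as activity and bone mass, and Section 2.5.2 makes them secondary outcomes. If a difference appears on self-reported activity, screen time, attitudes, competence or non-cognitive skills, a reader relying on Section 2.9 would discount expectation or socially desirable answering as an explanation. The design does not earn that assurance.

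**Working it through.** No figure in the plan depends on this point, so there is nothing to recompute. The check sets the sections against one another.

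**1. Does the disclosure reveal the arm?** Section 2.9's own parentheses equate going first with the intervention group and going later with the wait-list control. A child told which applies has been told the arm. What was withheld is the existence of a comparison. Not knowing of the comparison is different from not knowing one's own condition.

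**2. Could a child have been unaware of the condition in practice?** Under Sections 2.4.1 to 2.4.3, intervention children each received a small manual, met new activities week by week over 21 weeks, kept challenge cards with a rank that rose or fell, recorded one another, and watched a video. Under Section 2.4.4, control children "continued their routine school life and only underwent evaluation similar to the intervention group". The nature of the programme, which Section 2.9 gives as the reason teachers could not be blinded, applies equally to the children doing it.

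**3. Did this hold at every follow-up?** Section 2.4.4 places the wait-list programme after the final evaluation in December 2019. At each follow-up the control children had therefore not yet had the activity and the intervention children had begun or finished it. Section 2.8 says randomisation followed baseline collection, so baseline reports are unaffected. The follow-up reports are not, and analysing change from baseline does not remove a bias that enters only at follow-up.

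**4. Who assesses each outcome?**

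| Outcome | Role | Assessor | Aware of condition? |
|---|---|---|---|
| Stiffness index | primary | research assistants | no, as stated |
| MVPA from the wrist device | primary | device | not applicable |
| Self-reported activity and sedentary behaviour | secondary | child | yes |
| Depressive symptoms | secondary | child | yes |
| Social health, including non-cognitive skills | secondary | child | yes |

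The assessor-bias conclusion is reasonable for the first two rows and not for the other three.

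**5. Is there a route to differential reporting?** The video in Section 2.4.3, shown to the intervention group, teaches that everyday actions such as standing and walking count as exercise. It could change how those children answer activity and attitude items without any change in behaviour. The documents do not show that it did.

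**6. How many measures are exposed?** From Sections 2.6.2, 2.6.5 and 2.6.6, counting subscales separately: activity items 3, screen time (weekday and holiday) 2, depression scale 1, attitudes 2, stage of change 1, competence factors 3, school connectedness 1, personality dimensions 5, non-cognitive skills 3. The sum is 3 + 2 + 1 + 2 + 1 + 3 + 1 + 5 + 3 = 21. Counting screen time, competence and personality once each gives 3 + 1 + 1 + 2 + 1 + 1 + 1 + 1 + 3 = 14.

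**The case against.** The best defence is that the children knew their schedule but not that two groups were being compared. Whole schools were randomised, so a child did not see classmates treated differently. This partial masking could weaken expectation effects and deserves to be reported. It stands as a description, but it does not amount to blinding to allocation.

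A reader might infer that self-report made assessor bias worse. The documents do not support that. Self-report removes a third-party rater in a setting where teachers could not be blinded, the scales for grit, self-esteem and depressive symptoms are self-report instruments here, and no blinded alternative is described. The error is to count self-report as a safeguard, not to use it.

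A reader might also infer that the whole assessor-bias sentence should go, or that the primary results are undermined. Neither follows. The sentence is sound for bone mass and for device-measured activity, and Sections 2.5.1 and 2.5.2 already make device-measured MVPA primary and self-reported activity secondary. Knowing one's condition may still change behaviour, and so MVPA itself, but that is not assessor bias.

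The depression scale comes from a routine annual survey (Section 2.6.5), which weakens the case for trial-specific answering on that outcome. It does not remove it, because the July 2019 respondents knew what they had received. Finally, the Discussion does acknowledge error in self-report. Error unrelated to arm and error that differs by arm have different consequences, however, and only the second can by itself create an apparent effect. The caveat does not mention the second.

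**Conclusion.** The point holds in limited form. Section 2.9 states a blinding property for the children that the design does not have, and it extends an assessor-bias safeguard to outcomes assessed by respondents who knew their condition. The self-reported secondary outcomes are affected, 14 to 21 measures by the two counts above. No primary outcome is self-reported, and the sample size calculation does not depend on this point. The size and direction of any respondent bias cannot be derived from the documents.

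The conclusion rests on taking Section 2.9 at its word about what children were told and Section 2.4 at its word about what each group experienced. It assumes nothing about whether the children in fact answered differently.

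**What to change.** - **Section 2.9, children and teachers:** state that neither was blinded to the condition received, and that children were not informed of the group comparison.
- **Section 2.9, assessors:** limit the assessor-bias statement to bone mass, measured by staff unaware of allocation, and to device-measured activity.
- **Section 2.9 and the Discussion's limitations:** add that self-reported activity and sedentary behaviour, mental health and social health were assessed by unblinded respondents, are open to differential reporting as well as measurement error, and that effects on them are to be interpreted as supportive.

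The cost is wording and a less favourable blinding statement. No data collection, outcome or analysis has to change.

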### 2.10. Statistical Analysis

For inter-group comparisons of characteristics at baseline, independent t-tests and chi-square tests will be used for continuous and categorical variables, respectively. Missing values will be complemented using the multiple imputation method, which is integrated using Rubin’s formula [42], by creating 20 datasets under the assumption of the missing measurement mechanism of missing at random (intention-to-treat). To evaluate the effect of the intervention programme, a general linear mixed model will be employed for the analysis of continuous variables. Sensitivity analysis will be conducted for complete case analysis excluding data with missing values. Regarding the analysis of dichotomous secondary outcomes, the intervention effect will be examined by comparing the odds ratio estimated using multi-level (logistic model) regression analysis. Additionally, subgroup analysis will be performed in the population disliking exercise or precontemplation stage of transtheoretical model of behaviour change. All statistical analyses will be performed using Stata SE version 15.1 (StataCorp, Spring, TX, USA).

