### 2.7. Sample Size

The sample size was calculated based on the effect sizes (d = 0.50) derived from our previous study [29]; for example, the sample size was determined to detect a mean difference of five SI between the intervention and control groups with a standard deviation (SD) of 10 SI, and a mean difference in MVPA of 10 min/day with a SD of 20 min. A total of 63 children were required per group to detect a change in effect size with the alpha level set at 0.05 and power at 0.80.

To account for clustering, the required sample size of 63 children was adjusted by a design effect of 1 + (m − 1) ρ, where m is the average number of children per cluster and ρ is the intra class coefficient (ICC). We estimated that each school had 20 children and an ICC of 0.05. Using these estimates, the total required sample size was found to be 246 children (63 × (1 + (20 − 1) × 0.05 × 2 groups)). Furthermore, we assumed that 70% of the schools and 90% the children would accept participation, and 10% would drop-out during the study period. Therefore, it was assumed that at least 433 children were needed. Therefore, we recruited children from the 4th and 5th grade of all schools in Koshu City (13 schools, 511 children).

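### With nine randomised schools, the models named in section 2.10 carry no few-cluster correction; against a normal reference, type I error would be about 7 to 13% at the plan's ICC of 0.05

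*Protocol article*

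**What the plan says.** Section 2.8 (Randomisation) makes the school the unit of allocation: "Randomisation was conducted at the school level after baseline data were collected". It gives the number of schools: "This study was conducted in nine schools (18 classes, one class in each 4th and 5th grade; Figure 1". It also describes the matching: "These schools were matched by size (total number of children) and region (Enzan or Katsunuma area) into four pairs". The one remaining school, the smallest, was randomised singly, so the split is 4 against 5.

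Section 2.10 (Statistical Analysis) gives the effect analyses. For continuous outcomes, which include both primary outcomes: "To evaluate the effect of the intervention programme, a general linear mixed model will be employed for the analysis of continuous variables". For dichotomous secondary outcomes: "the intervention effect will be examined by comparing the odds ratio estimated using multi-level (logistic model) regression analysis". Missing values are handled with 20 imputed datasets combined by Rubin's formula. The section names no estimator, reference distribution, degrees-of-freedom method, cluster-level test or role for the pairs.

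Section 2.7 (Sample Size) sets the operating characteristics, "with the alpha level set at 0.05 and power at 0.80", and the clustering assumption: "We estimated that each school had 20 children and an ICC of 0.05". The Discussion admits that the clusters were small, but does not raise the small number of them.

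**The concern.** Treatment varies only between schools. Information about the error of the treatment effect therefore comes from nine units, however many children are measured. An unmatched comparison of 4 against 5 schools has 9 − 2 = 7 school-level degrees of freedom; a comparison within four pairs has 4 − 1 = 3. A normal critical value of 1.96 treats the between-school variance as if it were well known. ML adds a second problem, because it tends to estimate that variance too low with so few schools.

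Both primary outcomes go through the linear mixed model, and the dichotomous secondary outcomes through its logistic counterpart. If the reference distribution is wrong, intervals are too short and p-values too small, and the 0.05 of section 2.7 is not the level at which the trial is tested.

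**Working it through.** **Inputs from the article.** Nine schools, 4 v 5 (2.8). ICC 0.05 and 20 children per school (2.7). Alpha 0.05 and power 0.80 (2.7). Effect: "a mean difference of five SI between the intervention and control groups with a standard deviation (SD) of 10 SI", so d = 0.5. As an upper value for school size, 511/13 = 39.3 children per school (2.7). The realised school sizes are not in the text available. **Assumptions.** Two-sided test, a school random intercept, one change score without covariates, no imputation effect in the simulations, and 30% prevalence for a binary outcome.

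**The plan's own figure.** n per group = 2(1.96 + 0.842)²/0.5² = 62.8, so 63. Design effect = 1 + 19 × 0.05 = 1.95. Total = 63 × 1.95 × 2 = 245.7, so 246. Then 246/(0.7 × 0.9 × 0.9) = 433.9, against the stated 433. The figures reproduce. The 63 comes from normal quantiles (a t-based calculation gives 63.8), and the number of schools does not enter.

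**Closed form.** Using 1.96 when the statistic follows t:
- 7 df (pairs ignored): P(|t| > 1.96) = 9.1%. The correct critical value is 2.365; 1.96/2.365 = 0.83, so the interval is 17% too short.
- 3 df (four-pair comparison): P(|t| > 1.96) = 14.5%. The correct critical value is 3.182.

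**Simulation under no effect, linear model, ICC 0.05** (20,000 runs per row, Monte Carlo SE about 0.2 points):

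| School sizes | ML, z | REML, z | REML, t on 7 df | School means, t on 7 df |
|---|---|---|---|---|
| 20 each | 10.3% | 7.8% | 3.9% | 5.0% |
| 39 each | 12.0% | 8.7% | 4.7% | 5.2% |
| unequal, mean about 20 | 11.4% | 8.2% | 4.2% | 4.7% |
| unequal, mean about 39 | 13.0% | 9.1% | 4.9% | 4.7% |

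ML with t on 7 df still gives 5.4 to 7.4%, so the estimator matters as well as the df.

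**Logistic model, ICC 0.05** (1,500 runs, Monte Carlo SE about 0.6 to 0.9 points): with z, 7.4% at 20 per school and 10.8% at 39; with t on 7 df, 2.8% and 5.5%.

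**Sensitivity to ICC, tested against z:**

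| ICC | ML | REML | Logistic |
|---|---|---|---|
| 0 | 4.4 to 4.8% | 3.8 to 4.1% | not run |
| 0.01 | 6.2 to 8.0% | 5.0 to 6.3% | not run |
| 0.02 | 8.0 to 10.5% | 6.4 to 7.9% | 5.8 to 7.5% |
| 0.10 | 12.3 to 13.3% | 9.0 to 9.4% | 10.9 to 12.8% |

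**Pooling.** Classical Rubin df = (M − 1)/λ², where λ is the fraction of missing information. With M = 20 and λ = 0.10 (assumed, in line with the 10% drop-out in 2.7), df = 19/0.01 = 1,900 and the critical value is again 1.96. For λ from 0.05 to 0.30, the error against a true 7 df stays at 8.9 to 9.1%. A df correction made within each imputed dataset is therefore lost at pooling unless the pooling rule also uses the school-level df.

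**The case against.** The strongest reply is that the article never commits to large-sample tests. ML, z and 1.96 appear nowhere in section 2.10, REML with Kenward-Roger is itself a general linear mixed model, and a condensed article may leave the estimator and df to an analysis plan that is not shown. This stands in part. A reader might infer that the plan has chosen a z test and so doubles its error on every outcome; the text does not support that. At the plan's own inputs (20 children, ICC 0.05), REML and logistic give 7.8% and 7.4%, about 1.5 times nominal. No outcome-specific ICC is given, and at ICC 0 there is no inflation.

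It does not dispose of the point. Section 2.10 goes as far as the number of imputations, the pooling formula, the missingness mechanism and the software version. With nine schools, the reference distribution decides whether 0.05 means 0.05. Of the methods that are stated, the pooling rule in its classical form leads to a normal reference, although the article does not say which df version of Rubin's formula is meant.

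**Conclusion.** The point holds conditionally. Nothing in section 2.10 has to be withdrawn, since the model classes suit the design. But in their ordinary form with classical Rubin pooling they do not hold the 0.05 level with nine schools. At ICC 0.05, and with 20 to 39 children per school, type I error is about 10 to 13% for ML, 8 to 9% for REML and 7 to 11% for the logistic model. An unconditional claim that the error doubles fits ML and the closed-form 9.1%, but not REML or the logistic model at 20 children per school, and not a very small ICC. The figures ignore the pairs. If the pairs are modelled, the df fall towards 3 and a normal reference is worse (14.5% in closed form).

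**What to change.** Add a few sentences to section 2.10:

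- Continuous outcomes: REML with a school random effect and Kenward-Roger or Satterthwaite degrees of freedom. State whether the pairs are in the model: about 7 df if they are not, fewer (3 for a pure four-pair comparison) if they are.
- Binary outcomes: a t-test on school-level summaries, or the multilevel logistic model with between-within df. The latter is approximate: with t on 7 df, the simulated error at ICC 0.10 was 5.3% (20 per school) and 6.8% (39 per school).
- Imputation: include school in the imputation model so that the ICC is preserved. Pool the 20 datasets with a small-sample df built on the school-level complete-data df.
- Do not rely on a permutation test alone. If the single school is randomised independently of the pairs, there are 2⁴ × 2 = 32 allocations, so the smallest two-sided p is 2/32 = 0.0625.

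The work is small: text and model options. The statistical cost is real. Intervals widen by a factor of 2.365/1.96 = 1.21 at 7 df. For d = 0.5 and ICC 0.05, with SE = √[(0.05 + 0.95/m)(1/4 + 1/5)], power on 7 df is about 54% at m = 20 and 65% at m = 39. The normal reference shows 67% and 78%, but only because its type I error is inflated. If the ICC is close to zero, REML with t on 7 df is conservative (error about 1.3 to 1.5% at ICC 0), whereas the t-test on school means stays at about 4 to 5%.

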### 2.4. Interventions

#### 2.4.1. Active Play Programme

An active play programme was conducted in each elementary school for six months (from 15 January 2019 to 28 June 2019). The intervention required the children (≥2) to jump for approximately 10 s per session, at least five times a day (approximately 1 min/day). These short periods of activity were designed to be easy and enjoyable for everyone. Excluding the spring break, the intervention period lasted for 21 weeks. The participants performed three types of activities during the first week, with a new type of activity added each week to prevent the children from getting bored, providing a total of 24 activity types. Additionally, the activities were to involve any of the elements of the four categories of games distinguished by Caillois: Agon (competition), Alea (luck/chance), Mimicry (mimesis), and Ilinx (vertigo) [24]. To explain each activity, an instruction manual sheet (Figure 2), describing the method and illustration, was placed in each classroom. Moreover, a miniature version of the same instruction manual was distributed to each child by the homeroom teacher, and each child understood how to perform the activity themselves. However, since this programme aimed at encouraging children to play spontaneously, the classroom teacher was informed not to enforce an activity if the children had not implemented it. 

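### The stated complete-case sensitivity analysis does not relax missing at random, so its agreement with the primary imputation would say nothing about informative loss of the December 2019 MVPA outcome

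*Protocol article*

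**What the plan says.** Section 2.10 fixes three things:

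- Primary handling of missing data: "Missing values will be complemented using the multiple imputation method, which is integrated using Rubin’s formula".
- The assumption behind it, and its label: "by creating 20 datasets under the assumption of the missing measurement mechanism of missing at random (intention-to-treat").
- The check on it: "Sensitivity analysis will be conducted for complete case analysis excluding data with missing values".

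For continuous outcomes, "a general linear mixed model will be employed for the analysis of continuous variables".

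Section 2.7 allows for loss: "we assumed that 70% of the schools and 90% the children would accept participation, and 10% would drop-out during the study period". Primary MVPA is the change from baseline to the one-year follow-up (section 2.5.1), which Table 1 places in December 2019. The programme ended on 28 June 2019 (section 2.4.1). Tracker data are also collected in February and July 2019 (section 2.6 and Table 1). The Discussion lists limitations, but informative missing data is not among them.

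**The concern.** A sensitivity analysis for missing data should vary the assumption most open to doubt. Here that is missing at random: given what was observed, a child without December data is taken to resemble a child in the same arm with data. Complete-case analysis does not loosen this. It usually uses less of the observed information and so needs a stricter condition.

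The exposed outcome is tracker MVPA. It needs a wrist device worn day and night for 10 days, in a round held some months after the programme ended. If inactive children supply fewer usable data, and more so in one arm, the treatment difference is biased. A report that imputation and complete-case agree would then be read as robustness when it is not evidence of that.

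**Working it through.** **Inputs.** From section 2.7: MVPA target 10 min/day with SD 20; SI target 5 with SD 10; alpha 0.05; power 0.80; 20 children per school; ICC 0.05; drop-out 10%. Assumed, because the article does not give them: missing rates of 20% and 30%, correlations between visits, and the way missingness depends on activity.

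**1. The plan's own figures reproduce.** With d = 0.50 and a two-sided test, n = 2 × (1.96 + 0.84)² / 0.50² ≈ 63 per group. The design effect is 1 + 19 × 0.05 = 1.95. The total is 63 × 1.95 × 2 = 245.7, rounded to 246. Then 245.7 / (0.70 × 0.90 × 0.90) = 433.3, against 433 stated. The 10% is therefore the plan's working drop-out rate.

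**2. What each analysis assumes for a missing December value.**

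- Multiple imputation: missingness is unrelated to the unseen value, given arm and everything in the imputation model.
- Complete-case: missingness is unrelated to the unseen value, given only the covariates in the analysis model, or is completely at random.

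The second condition is equal to the first or stricter. Neither allows missingness to depend on the unseen value itself.

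**3. Simulated false benefit (MVPA, min/day).** True effect 0 and SD 20. Missingness is random in the control arm; in the intervention arm it rises as activity falls (log-odds 1.5 per SD). The analysis model adjusts for baseline. Clustering is left out. Repeating the runs with another random seed moves entries by about 0.1.

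| Intervention-arm loss depends on | Imputation uses | Correlation | 10% missing: complete-case / imputation | 20% | 30% |
|---|---|---|---|---|---|
| unseen December MVPA | baseline only | 0.5 | 1.87 / 1.88 | 3.45 / 3.54 | 5.07 / 5.23 |
| unseen December MVPA | baseline, February, July | 0.6 | 1.5 / 1.2 | 2.9 / 2.5 | 4.3 / 3.7 |
| observed July MVPA | baseline, February, July | 0.6 | 0.6 / about 0 | 1.0 / about 0 | 1.6 / about 0 |

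In the first two rows both analyses are wrong in the same direction. In the third, missing at random holds, imputation is right, and the two analyses separate.

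**4. Size against the design.** The design standard error for MVPA is 20 × √(2/63) = 3.56 min/day. At 10% missing, a false benefit of 1.2 to 1.9 is 12% to 19% of the 10 min/day target and 1.2/3.56 = 0.34 to 1.9/3.56 = 0.53 of a standard error.

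**5. What a delta shift would show.** If imputed intervention values are lowered by δ, the estimate falls by p × δ, where p is the proportion missing in that arm. Significance is lost near 1.96 × 3.56 = 6.98 min/day. Holding the standard error fixed, the tipping shift is (estimate − 6.98) / p.

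| Estimate | p = 10% | p = 20% | p = 30% |
|---|---|---|---|
| 10 min/day (planned) | 30.2 | 15.1 | 10.1 |
| 8 min/day (assumed) | 10.2 | 5.1 | 3.4 |

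For SI at the planned effect of 5, the shifts are half the first row: about 15, 7.5 and 5 SI.

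**The case against.** **An analysis plan may add more.** The article is a condensed account, and it does not say that complete-case is the sole check. A reader might infer that no missing-not-at-random analysis will be done. The article does not support that: it shows only that the check it names cannot do this job. That narrower statement stands, because the choice is written into section 2.10.

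**The two analyses need not give the same answer.** A reader might infer that imputation and complete-case always share one bias. That holds nearly exactly only when imputation uses baseline alone. The article does not restrict the imputation model, and activity and related questionnaire items are collected at all four visits. With interim data the two can differ, and where loss depends on July activity the comparison is informative. Disagreement can therefore be useful; agreement still cannot exclude dependence on the unseen December value.

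**The effect is small at the planned rate.** This stands. Larger biases come from 20% and 30% missing, which are assumptions, as is loss that is informative in one arm only.

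**The mechanism is uncertain.** A reader might take the instruction that "the classroom teacher was informed not to enforce an activity if the children had not implemented it" as a cause of drop-out. It concerns adherence: a child who stops jumping is still in class and can be measured. The programme had also ended before the December round, and trackers are charged in class and synced by investigators (section 2.6.1). The article neither establishes nor excludes informative loss, which is why a check is wanted.

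**Bone mass is less exposed.** SI is taken around the routine school health check-up (section 2.6), and tracker non-wear cannot make it missing. This also stands.

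**Conclusion.** The point holds in a limited form. The check named in section 2.10 does not test the assumption on which the primary MVPA analysis rests, so agreement between the two analyses should not be presented as evidence against informative missingness. Under the assumed mechanisms, the undetected bias is about 1 to 2 min/day at 10% missing. That alone would not overturn a result at the planned effect, since missing intervention children would have to lie about 30 min/day (1.5 SD) below their imputed values. It could matter for a smaller estimate: at 8 min/day and 10% missing, a shift of about 10 min/day (0.5 SD) is enough. It could also matter if unusable tracker data run well above 10%, a rate the article does not forecast.

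This is a cheap improvement to the plan, not a flaw that invalidates the primary analysis.

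**What to change.** In section 2.10, or in the analysis plan if it is still open:

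1. Keep multiple imputation under missing at random as primary, and state that the imputation model includes tracker activity from the February and July visits.
2. Keep complete-case as a supplementary analysis, not as the test of the missing-data assumption.
3. Add a delta-adjusted tipping-point analysis for primary MVPA. Lower the imputed values, for example from 0 to −20 min/day, once in the intervention arm only and once in both arms. Report the shift at which the conclusion changes, or that it does not change within the range. A common shift in both arms moves the estimate only as far as missingness differs between arms, so show missingness by arm and visit beside it.
4. Apply the same to SI, with lower priority.

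The cost is one sentence, a few lines of code on the 20 imputed datasets, and one table. No new data are needed. The price is that the reported result may look less reassuring.
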